## Abstract

**Background:**

Low health-related physical fitness in college students is a risk factor for future development of cardiovascular diseases at later stages in life, but appropriate exercise is one of the main determinant factors of health-related physical fitness. Previous studies have showed that Baduanjin exercise is beneficial in improving sleep quality, mental health, body flexibility, and body physique. However, the evidence is unclear whether Baduanjin exercise can be recommended as an effective exercise to promote health-related physical fitness of college students.

**Methods/design:**

One hundred twenty college students will be recruited and randomly allocated to either the Baduanjin exercise or the control group at a ratio of 1:1. The students in the Baduanjin exercise group will receive a 12-week supervised Baduanjin exercise training intervention with a frequency of 1 h each day and 4 days per week, while those in the control group will not receive any specific exercise intervention and will be informed to maintain their original lifestyle for 12 weeks. The primary outcome of health-related physical fitness involving measurements of body flexibility, muscular strength, cardiopulmonary fitness, and body endurance will be measured at baseline and after the 12-week intervention period. Mixed linear models will be used to analyze the effect of the Baduanjin exercise intervention on the health-related physical fitness of college students.

**Discussion:**

This is the first trial to evaluate the effects of Baduanjin exercise on health-related physical fitness in college students. If the results are as expected, they will provide evidence of Baduanjin exercise in promoting health-related physical fitness in young adults.

**Trial registration:**

Chinese Clinical Trial Registry, ChiCTR-IOR-17013011. Registered on 17 November 2017.

**Electronic supplementary material:**

The online version of this article (10.1186/s13063-019-3672-1) contains supplementary material, which is available to authorized users.

## Background

Health-related physical fitness is defined as the capability of an individual to carry out his everyday activities without excessive fatigue and with enough spare energy to enjoy free time and to solve unusual situations [1, 2]. Health-related physical fitness is also regarded as an integrative measure of most body functions, such as musculoskeletal, cardiorespiratory, hematocirculatory, endocrine-metabolic, and psychoneurological functions [3, 4].

With China’s rapid economic development and transitions in lifestyle, the health-related physical fitness of its adolescent and students has undergone a significant decline. For example, the rates of overweight and obesity in 2010 were estimated to be 9.9% and 5.1%, respectively, in school-aged adolescents, and neared those of developed countries [5]. Furthermore, the measure of physical endurance of students was not optimistic, and the failure rate of endurance running was up to 23.7% in male students and 19.6% in female students [6]. According to reports from National Student Physical Fitness Research, the health-related physical fitness of students in China gradually declined from 1985 to 2005 [7]. This tendency was curbed in 2010, but a significant improvement was still not achieved [8, 9].

College students are in a critical period of growth and development that connects high school with adulthood [10]. They will complete the transition to autonomy by independently making decisions and developing behavior patterns, many of which will continue throughout their lives [11]. Due to higher study pressures and the pervasive presence of the Internet and smartphones, college students are prone to developing unhealthy behaviors and habits, such as physical inactivity, poor diet, and alcohol misuse [12, 13]. Low health-related physical fitness in young adults is a risk factor for the future development of cardiovascular disease, which has globally increased in the last five decades. This represents a public health issue in the young population about which we should be concerned [14, 15].

Health-related physical fitness is partially genetically determined, but it can be strongly influenced by environmental factors [16, 17]. Appropriate exercise is one of the main determinant environmental factors [13, 18]. Regular exercise can not only increase the level of physical activity and correct the deviation of health-related behavior, it can also aid in the development of a healthful lifestyle [19, 20]. Qigong is the general name given to many traditional Chinese mind–body exercises [21]. It is a holistic system of coordinated body posture and movement, breathing, and meditation used for health, spirituality, and martial arts training, and it has been practiced for health promotion in China for thousands of years [22–24]. Baduanjin exercise, one of the most common forms of Qigong, consists of eight separate, delicate, and smooth exercise movements; each section brings certain function-enhancing benefits to different physical parts of the body or particular organs [25]. Through concepts and respiratory adjustments designed to achieve self-psychosomatic regulation, Baduanjin exercises emphasize the meaning of “Qi” and “form,” resulting in a comprehensive exercise to achieve physical and mental harmony [25]. Studies have shown that Baduanjin training is helpful for older people with physical and mental disorders such as anxiety, hyperlipidemia, spinal problems, osteoarthrosis, and type 2 diabetes [26–28]. Several studies also indicated that Baduanjin exercise has a potential benefit in improving physical function in young adults [29–31]. Our previous study indicated that a 12-week regimen of regular Baduanjin training could improve the lower limb proprioception and flexibility of college students [32, 33], but other parameters of health-related physical fitness such as muscular strength, endurance, cardiovascular fitness, and body composition were not observed. Therefore, the evidence is unclear whether Baduanjin exercise can be recommended as an effective exercise to improve the health-related physical fitness of young adults. The purpose of this trial is to evaluate the effects of Baduanjin exercise on health-related physical fitness of college students by a randomized controlled trial with a rigorous design.

## Methods/design

### Study aim

The aim of this trial is to evaluate the effectiveness of a 12-week Baduanjin exercise intervention on the health-related physical fitness of college students.

### Study design

This study is a randomized, parallel-group controlled trial to evaluate the effectiveness of a Baduanjin exercise intervention on the physical fitness of college students. A total of 120 eligible college students from the Shanghai University of Medicine and Health Sciences (SUMHS) will be recruited and randomly allocated to either the Baduanjin exercise group or the control group at a ratio of 1:1. Participants in the Baduanjin exercise group will receive a 12-week supervised Baduanjin exercise training intervention with a frequency of 1 h each day and 4 days per week, while those in the control group will not receive any specific exercise intervention and will be informed to maintain their original lifestyle for 12 weeks. Primary and secondary outcomes will be measured at baseline and after the 12-week intervention period. The participant flow for this trial is presented in Fig. 1. The present protocol follows the Standard Protocol Items: Recommendations for Interventional Trials (SPIRIT) guidelines and fulfills the SPIRIT checklist (see Additional file 1).

**Fig. 1 Fig1:**
[figure not shown]
Proposed participant flow (Consolidated Standards of Reporting Trials [CONSORT] diagram)

### Sample size calculation

The primary outcome of this trial involves global health-related physical fitness ability changes which are assessed using composite points of health-related physical fitness. According to study data [34], the mean and standard deviation of a composite point in the health-related physical fitness of college students were measured as 55 points and 12.5 points, respectively. A sample size of 100 will have 80% power to detect a difference in a composite score of health-related physical fitness of 5.0% and an α of 0.05 for a two-sided significance level. Assuming a maximum loss to follow-up of 20%, a total of 120 subjects was necessary.

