### Statistical analysis

Analysis of data in this trial will be performed by a statistician who is not involved in the trial. In descriptive analysis of the sample, continuous variables will be expressed by using the mean and standard deviation for normal distributions, and the median and interquartile range for non-normal distributions. Normality will be tested using the Kolmogorov–Smirnov test. Appropriate transformations will be applied in cases of non-normal distribution. Categorical variables will be expressed as proportions with their standard error.

Baseline characteristics between groups will be compared using the *t* test or Mann–Whitney test for continuous variables and Pearson’s χ-squared or Fisher’s exact test for categorical variables. If incomparability appears, the inequality factors will be treated as confounding variables in the final efficacy analysis.

For comparison of primary and secondary outcomes between groups, a *t* test or non-parametric tests will be used for continuous data, and Pearson’s χ-squared or Fisher’s exact test for categorical data at baseline and after intervention; the between-group differences (treatment effects) will be analyzed by using mixed linear models with restricted maximum likelihood using the group-by-time interaction terms. Analysis of the outcomes will be performed on the basis of the intention-to-treat (ITT) population. All participants who have been randomized will be included in the final analysis irrespective of compliance or withdrawal from the program. Full information maximum likelihood estimation will be employed for missing data.

AEs will be listed and analyzed using a χ-squared test or Fisher’s exact test. Severe AEs will be listed and described in detail.

All data will be analyzed with SPSS 21.0 (IBM, Chicago, IL, USA) software packages. Statistical significance is defined as a two-sided *P* value of < 0.05.

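### The stated 80% power with 100 students does not follow from the sample size inputs, and it is not established for the planned group-by-time test

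*Protocol article*

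**What the plan says.** All the inputs are in the Protocol article under Sample size calculation.

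- Outcome: "The primary outcome of this trial involves global health-related physical fitness ability changes which are assessed using composite points of health-related physical fitness".
- Spread: "the mean and standard deviation of a composite point in the health-related physical fitness of college students were measured as 55 points and 12.5 points".
- Claim: "A sample size of 100 will have 80% power to detect a difference in a composite score of health-related physical fitness of 5.0" (a percent sign follows the number), with "an α of 0.05 for a two-sided significance level".
- Attrition: "Assuming a maximum loss to follow-up of 20%, a total of 120 subjects was necessary".

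Study design says that the 120 students are "randomly allocated to either the Baduanjin exercise group or the control group at a ratio of 1:1" and that outcomes are taken at baseline and after 12 weeks. Statistical analysis attaches the term treatment effects to "mixed linear models with restricted maximum likelihood using the group-by-time interaction terms". The same section also plans a t test or non-parametric comparison of the groups at each of the two visits.

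**The concern.** There are two separate problems.

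First, the number, the SD and the difference should together return the stated power. Allocation is 1:1 and 120 is the total, so 100 evaluable students means 50 per group. An SD of 12.5 is large relative to a difference of 5 points, and more so relative to 2.75 points, the other reading of 5.0%.

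Second, a mean of 55 with SD 12.5 describes the score of a student at one time, whereas the outcome is worded as change. With two visits and complete data, the group-by-time term is the difference between groups in mean change. Its variance depends on how strongly a student's week-12 score follows the baseline score. Neither an SD of change nor a correlation appears.

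At stake is the one figure that says what the trial was built to detect. If a non-significant interaction is reported beside a claim of 80% power, readers may take it as fair evidence against a 5% effect when the trial may have had much less power for it.

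**Working it through.** **Inputs from the article.** SD 12.5 and mean 55; two-sided alpha 0.05; 100 evaluable, 1:1, so 50 per group; difference 5.0%, read as 5 points or as 0.05 × 55 = 2.75 points; 20% loss; 120 randomised.

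**Assumptions, not in the article.** SD 12.5 at both visits; correlation rho between baseline and week 12, varied.

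**Step 1: try to reproduce 80%.** Two-sample t test (noncentral t), standardised difference d/SD.

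| Difference | d/SD | Needed per group for 80% | Power at 50 per group | Power at 100 per group |
|---|---|---|---|---|
| 5 points | 0.40 | about 99 | 51% | 80% |
| 2.75 points | 0.22 | about 325 | 19% | 34% |

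The normal approximation agrees to within about one percentage point (51.6% and 19.5% at 50 per group). A one-sided test at 0.05 does not rescue the figure: 64% and 29% by the normal approximation. For a two-group comparison, the stated 80% is recovered only with about 100 per group and a difference of 5 points. That suggests that a per-group number was used as the total, though the article does not show how 100 was obtained.

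**Step 2: the planned test.** For a difference in mean change,

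SD_change = 12.5 × √(2(1 − rho)).

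For example, rho 0.7 gives 12.5 × √0.6 = 9.68. At 50 per group:

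| rho | SD_change | Power, 5 points | Power, 2.75 points |
|---|---|---|---|
| 0.3 | 14.79 | 39% | 15% |
| 0.5 | 12.50 | 51% | 19% |
| 0.7 | 9.68 | 73% | 29% |
| 0.75 | 8.84 | 80% | 34% |
| 0.8 | 7.91 | 88% | 41% |
| 0.9 | 5.59 | 99% | 68% |

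Power of 80% at 50 per group needs SD_change of 8.84 (rho about 0.75) for 5 points, or 4.86 (rho about 0.92) for 2.75 points.

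**Step 3: separate the two problems.** At rho 0.5, SD_change equals 12.5, so using the level SD costs nothing there; the 51% in that row comes entirely from having 50 per group. To isolate the level/change mismatch, take the one setting that reproduces 80% (100 per group, 5 points). The change test then has 66% power at rho 0.3, 80% at 0.5, 88% at 0.6, 95% at 0.7 and 99% at 0.8. Taken alone, the level SD is neutral at rho 0.5, conservative above it and optimistic below it.

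**Step 4: attrition.** 100/(1 − 0.20) = 125, whereas 120 × 0.80 = 96, or 48 per group. At 48 per group the correlations needed for 80% rise slightly, to about 0.76 (5 points) and 0.93 (2.75 points). This is minor beside steps 1 and 2.

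**The case against.** The strongest reply has four parts.

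- The sentence that states the power speaks of a difference in a composite score, not in change, and names no test. Statistical analysis also plans a between-group comparison after the intervention, for which 12.5 is the right scale. This stands, and it means that the level SD is not wrong for every analysis in the plan. It does not save the 80%, because that comparison has about 51% or 19% power at 50 per group. Nor is it the analysis to which the article attaches treatment effects.
- A reader might infer that the 80% is correct for a one-visit comparison and fails only because the trial tests change. Step 1 rules that out: on the stated inputs the figure fits neither test.
- A reader might also infer that the trial is shown to have less than 80% power for its own test. The article does not support that. The correlation is unknown, and for 5 points a value of 0.75 or more gives at least 80% even at 50 per group. Nor does the level SD by itself push the power in a known direction.
- A condensed article may leave a correlation to the full protocol or analysis plan, and a confidence interval for the interaction will show how informative a null result is whatever was assumed. Both points are fair and limit the weight of the concern. They do not excuse a printed power figure that disagrees with the SD, number and difference printed beside it.

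**Conclusion.** The point holds in two parts of different strength.

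The firm part is arithmetic. SD 12.5, 100 students in total and two-sided 0.05 give about 51% power for 5 points or 19% for 2.75 points, not 80%. This rests only on the article's figures and on reading 100 as the total, as the 120 and the 1:1 allocation imply.

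The second part is that the 80% is not established for the group-by-time test. Over correlations from 0.5 to 0.9, power at 50 per group is 51% to 99% for 5 points and 19% to 68% for 2.75 points. Those ranges assume equal SDs of 12.5 at both visits and 50 complete pairs per group. The conclusion is that the claim cannot be verified, not that it is shown to be false for that test. The matter should be corrected, but it does not undermine the design or the planned analysis.

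**What to change.** In Sample size calculation:

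1. Give the target difference in points, so that 5.0% has one meaning.
2. Say whether 100 is the total or the number per group.
3. Give the SD of the 12-week change, or keep the level SD and state the assumed correlation. If the model is to adjust for baseline, the matching residual SD is 12.5 × √(1 − rho²).
4. Restate the power, or the detectable difference, for the group-by-time effect at the actual number of students, over a range of correlations such as 0.5 to 0.9.

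Enrolment should not change; the Trial status section reports that recruitment is complete. The cost is one recalculation and some rewording, with no new data. The downside is that a single 80% becomes a range that depends on an assumed correlation and may lie below 80%.

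### The stated 80% power with 100 students in total does not follow from the protocol's own inputs, which require 100 students per group for 5 points and 326 per group for 2.75 points

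*Protocol article*

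**What the plan says.** The Sample size calculation section of the protocol article sizes the trial on "global health-related physical fitness ability changes which are assessed using composite points of health-related physical fitness". It takes the mean and SD of the composite from a cited study; these "were measured as 55 points and 12.5 points, respectively". It then states: "A sample size of 100 will have 80% power to detect a difference in a composite score of health-related physical fitness of 5.0" percent, with "an α of 0.05 for a two-sided significance level". The allowance for attrition follows: "Assuming a maximum loss to follow-up of 20%, a total of 120 subjects was necessary".

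The Study design section confirms that the final figure covers both groups: "A total of 120 eligible college students" are to be recruited and allocated 1:1. The 100 before attrition is therefore also a two-group total, 50 per group.

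The Statistical analysis section estimates the treatment effect by a mixed linear model with a group-by-time interaction. The sample size section gives no correlation between baseline and 12 weeks and no SD of change.

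**The concern.** The article prints a complete set of inputs for a two-sample calculation together with a result, and the two do not agree. The stated 100 equals the number needed in each group for a 5-point difference, but it is used as the number for both groups together. In addition, the target carries a percent sign on an outcome scored in points. It may mean 5 points on the composite or 5% of the mean of 55, and the choice changes the required sample more than threefold.

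This calculation is the article's only justification for the trial's size. A reader who accepts 80% power will give a non-significant result more weight against a 5-point benefit than the stated inputs support.

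**Working it through.** **Inputs** (Sample size calculation and Study design sections): SD 12.5; mean 55; two-sided alpha 0.05; power 80%; 1:1 allocation; 100 before attrition and 120 after, both as totals.

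**Two readings of the target**
- 5 points: d = 5/12.5 = 0.40.
- 5% of the mean: 0.05 × 55 = 2.75 points; d = 2.75/12.5 = 0.22.

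**Attempt to reproduce the 100.** The normal approximation is n per group = 2(1.960 + 0.842)²/d².
- d = 0.40: 2 × 7.849/0.160 = 98.1, so 99 per group. The noncentral t gives 99.08, so 100 per group, 200 in total.
- d = 0.22: 2 × 7.849/0.0484 = 324.3, so 325 per group. The noncentral t gives 325.3, so 326 per group, 652 in total.

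The 100 appears only as a per-group number, and only for 5 points. A one-sided test does not rescue it: 78 per group would be needed for 5 points (normal approximation).

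**Attrition.** 120 = 100 × 1.2. A loss of 20% from 120 leaves 120 × 0.8 = 96, or 48 per group; keeping 100 would need 100/0.8 = 125. This gap is minor beside the main one.

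**Power if 12.5 is the SD of the compared quantity** (noncentral t, two-sided 0.05)

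| Analysed per group | 5 points | 2.75 points | Difference detectable with 80% power |
|---|---|---|---|
| 48 (120 less 20%) | 49% | 19% | 7.2 points |
| 50 (the stated 100) | 51% | 19% | 7.1 points |
| 60 (all randomised) | 58% | 22% | 6.4 points |

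**Power of the group-by-time contrast.** With two time points and complete data this contrast compares mean changes. If the SD is 12.5 at both times and the correlation is ρ, the SD of change is 12.5 × √(2(1 − ρ)). The article gives no ρ, so the values below are assumptions. For 5 points:

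| Assumed ρ | SD of change | Power, 48 per group | Power, 60 per group |
|---|---|---|---|
| 0.5 | 12.5 | 49% | 58% |
| 0.7 | 9.7 | 71% | 80% |
| 0.8 | 7.9 | 87% | 93% |

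Power of 80% for 5 points needs ρ of about 0.76 with 48 per group, 0.75 with 50 and 0.70 with 60. For 2.75 points with 50 per group it needs about 0.92.

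**If baseline were a covariate (ANCOVA)**, the SD would be 12.5 × √(1 − ρ²). Power for 5 points with 48 per group would be 61%, 78% and 90% at ρ of 0.5, 0.7 and 0.8. The article does not specify this analysis.

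**The case against.** The strongest case on the other side is that the trial compares changes. The sample size section speaks of changes in fitness and the analysis section uses a group-by-time contrast, so a high baseline/12-week correlation could bring actual power to 80% or above. That stands, and it limits the conclusion. A reader might infer that the trial simply has about 50% power. The documents do not support that: the figure holds only if 12.5 is the SD of the compared quantity, as it would be for 12-week scores alone or for change at a correlation of exactly 0.5. The objection does not rescue the printed figure, however. The 12.5 is given as the SD of a composite with mean 55, which is a level and not a change, and no correlation is stated.

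A second objection is that 48 per group is a floor. This is also fair. The article calls 20% a maximum loss, and all randomised students are to enter the analysis, with full information maximum likelihood for missing data. Even with all 60 per group, power on the stated SD is 58%.

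A reader might also conclude that the authors mistook a per-group number for a total. That is the likely cause, but the article does not say how 100 was obtained. A one-sample formula gives 7.849/0.160 = 49.06, so 50; applied once per group, it would also yield 100. The finding does not depend on the cause.

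Nor is this a detail left to a fuller document. The inputs and the result are both printed, and they disagree.

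**Conclusion.** Wrong as written. With SD 12.5 and two-sided alpha 0.05, 80% power needs 100 students per group for 5 points or 326 per group for 2.75 points, whereas the protocol has 100, raised to 120, for both groups together. On the stated SD, 96 to 120 analysed students give 49% to 58% power for 5 points and 19% to 22% for 2.75 points.

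These percentages assume two independent groups of equal size, a common SD of 12.5 for the compared quantity and no gain from baseline. What is established is that the 80% does not follow from the inputs. The true power of the planned contrast remains unknown without the correlation: over an assumed 0.5 to 0.8 it runs from 49% to 87% for 5 points with 48 per group.

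**What to change.** The Trial status section reports recruitment as complete, so this is a correction of wording with no extra enrolment.

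1. State the target difference in points, either 5 or 2.75.
2. Replace the 80% statement with the power that 96 to 120 analysed students give on the stated SD. For 5 points this is 49% to 58%, and 80% power applies to differences of about 7.2 points (96 students) down to 6.4 points (120 students).
3. Because the planned treatment effect is the group-by-time contrast, add its power over a range of correlations labelled as assumed. For 5 points with 48 per group: about 49% at 0.5, 71% at 0.7 and 87% at 0.8. Say that 80% needs about 0.76, or about 0.70 with all 60 per group. If the target is 2.75 points, give the corresponding figures for that difference.
4. If ANCOVA figures are shown (61%, 78% and 90% at the same correlations with 48 per group), label them as applying only if a baseline-adjusted analysis is adopted.

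The cost is one rewritten paragraph and a less favourable power statement.

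### The 20% dropout allowance is applied the wrong way round: 120 randomised leaves 96 after 20% loss, not the 100 the calculation requires

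*Protocol article*

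**What the plan says.** The section on sample size calculation in the protocol article takes two steps. The first fixes the requirement: "A sample size of 100 will have 80% power to detect a difference" on the composite fitness score, with "an α of 0.05 for a two-sided significance level". The second adds an allowance for dropout: "Assuming a maximum loss to follow-up of 20%, a total of 120 subjects was necessary".

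The study design section shows that 120 is the total randomised, not a per-arm number: "A total of 120 eligible college students from the Shanghai University of Medicine and Health Sciences (SUMHS) will be recruited and randomly allocated". The two arms are of equal planned size. The abstract repeats the 120. Nowhere does the article give another loss rate or another reason for 120.

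**The concern.** A dropout allowance should ensure that the required number of students still have outcome data after the assumed loss. The loss applies to everyone randomised, so the required number must be divided by the proportion retained. Going from 100 to 120 looks like 20% added to the completers instead.

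If so, the protocol promises protection at a 20% loss that its own total does not give, and any power claim tied to 100 students fails at the loss the plan names as its maximum. The protocol's limitations paragraph mentions clashes with other commitments and adherence in the exercise arm as possible problems, so some loss is a realistic prospect.

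**Working it through.** **Inputs (protocol article)**

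- Required number with outcomes: 100 (sample size section). It is not labelled as total or per arm, but the step to a total of 120 treats it as the total.
- Maximum loss: 20% (sample size section).
- Total randomised: 120, allocated 1:1 (study design).
- Composite score: mean 55, SD 12.5; difference 5.0%; two-sided 0.05; power 80% (sample size section).

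**Step 1: reproduce the stated total**

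100 × (1 + 0.20) = 120. This matches exactly.

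**Step 2: the correct inflation**

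n / (1 − d) = 100 / (1 − 0.20) = 100 / 0.80 = 125. Two equal arms need 126, or 63 per arm. The stated total is 5 short (6 for equal arms).

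**Step 3: what 120 delivers**

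- At 20% loss: 120 × 0.80 = 96, or 48 per group. That is 4 fewer than 100.
- Loss that still leaves 100: 1 − 100/120 = 16.7%, or 20 students lost. A 20% loss is 24 students.

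**Step 4: effect on power, taking the plan's 80% at face value**

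If 50 per group gave 80%, the standardised difference is 1.960 + 0.842 = 2.802. With 48 per group it becomes 2.802 × √(48/50) = 2.745. Power is then Φ(2.745 − 1.960) = Φ(0.785) = 78.4%, a loss of 1.6 percentage points.

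**Step 5: effect on power, using the stated SD**

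Two-sample t test, SD 12.5, no baseline adjustment, equal loss in both groups:

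| Reading of 5.0% | 50 per group | 48 per group | Change |
|---|---|---|---|
| 5.0 points | 50.8% | 49.2% | 1.6 points |
| 2.75 points (5% of 55) | 19.3% | 18.7% | 0.6 points |

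The normal approximation for 5.0 points gives 51.6% and 50.0%, the same change.

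**Step 6: does the starting 100 hold?**

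For 5.0 points, n per arm = 2 × (2.802 × 12.5 / 5.0)² ≈ 98.1, rounded up to 99, or 198 in total. So 100 resembles a per-arm number. That is a separate problem, but it bounds this one: if 100 was meant per arm, the inflated total would be 200/0.80 = 250, and the gap to 120 far larger than 5.

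**The case against.** The strongest reply concerns weight, since the arithmetic cannot be disputed.

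- **The effect is tiny.** On any reading, power changes by 1.6 percentage points or less, and no analysis or estimand changes. This stands.
- **It matters only near the ceiling.** Up to 16.7% loss, at least 100 remain, and the protocol pays an incentive after the final assessment to encourage retention. This also stands as a limit on the practical effect. It does not make the sentence true, because 20% is the loss the protocol claims to cover.
- **The 100 is itself unsupported.** Redoing the first step would change the number to be inflated, and the power figures near 50% come from that first step, not from dropout. This is fair: only the 1.6-point change belongs here. But the inflation formula would be wrong for any starting number.
- **Recruitment is complete**, so only wording can change. True, and the fix asks for no more than that.

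One possible defence does not help. The statistical analysis section includes all randomised students and uses full information maximum likelihood. Outcomes are measured only at baseline and 12 weeks, so a student lost before week 12 contributes a baseline value alone. The method keeps that student in the model but does not recover the missing 12-week information.

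**Conclusion.** The point holds. The stated total of 120 does not preserve 100 students at 20% loss. It leaves 96, and the total that would preserve 100 is 125 (126 with equal arms). The loss that 120 can absorb is 16.7%.

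The error is certain but minor: 4 students with outcomes, 5 or 6 randomised, and about 1.6 percentage points of power for a 5-point difference. Type I error and the validity of the estimates are unaffected.

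The head counts assume only that 100 is a total and that the 20% applies to those randomised. The power figures also assume equal loss in both groups. Those in Step 5 further assume the stated SD of 12.5, an unadjusted comparison and, for the headline figure, that 5.0% means 5.0 points.

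**What to change.** Replace the dropout sentence in the sample size section with one on these lines: *With 120 students randomised, 100 have 12-week outcomes if loss is at most 16.7%; at the assumed maximum loss of 20%, 96 (48 per group) do.* Base the corrected power statement on 96.

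Make the change together with a correction of the first step, so that the new sentence does not endorse 100 as an adequate total. That correction should say whether 5.0% means 5.0 points or 5% of the mean, and whether any baseline adjustment is assumed.

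The cost is one sentence and a slightly less favourable figure. No participants are added, and neither the conduct of the trial nor its analysis changes.
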